### 5.8. Blinding Methods and Measures to Protect Blinding

The allocated arm (active or sham rTMS) will not be documented in the medical record. Blinding will be maintained for the patients included and for investigators involved in participant inclusion and follow-up.

Two independent staff members will be designated to receive the randomization email and forward it to the rTMS operator. These individuals and the rTMS operator, who will be aware of the sham or active condition, will not be involved in the participant follow-up or evaluation. A sham coil producing the same noise, heat, clicks, and sensations as the active coil but without any magnetic pulses will be used.

### 5.9. Unblinding Procedures, If Applicable

If deemed essential, the investigator can request unblinding for a specific patient by contacting the DRCI and the DRCI project advisor, whose contact information is provided on the protocol cover page. In this trial, no emergency unblinding request is mandatory.

## 6. Procedure and Data Collection

### 6.1. Inclusion Procedure

Patients will be recruited during an appointment at a participating specialized trauma unit (trauma center). Patients may be either hospitalized or treated as outpatients. During the selection visit and prior to any research-related examination, the physician will propose the study to the patient, informing them about the objective, the nature of the constraints, the computerized processing of the data that will be collected during this research, and their rights of access, opposition, and rectification to these data. During this visit, the eligibility criteria will be verified by the investigator or co-investigator. An information form summarizing these points will be provided to the patient. If they are interested, informed consent will be signed, and the participant will be screened for inclusion and exclusion criteria. If a patient meets all the inclusion criteria and none of the exclusion criteria, they will be included in the study by the researcher.

A computer-generated randomization list (1:1) will be created by the Clinical Research Unit (URC) of Saint-Antoine Hospital (AP-HP). Randomization will be block-balanced and stratified on-site. The width of the blocks will not be disclosed to investigators. Randomization will be performed using a web interface (CleanWeb 2.0 Software, Telemedicine, Paris, France) at the inclusion visit or before the first rTMS session by the rTMS operator. The allocated arm (active or sham rTMS) will not be included in the medical records. The blinding of the allocated treatment will be applied to both the included patients and investigators involved in the patient’s inclusion and follow-up. The operator performing the rTMS will be the only one aware of the sham or active condition. This operator will not be involved in the patient’s follow-up and evaluation.

### 6.2. Patient Recruitment

In the event of recruitment challenges, a recruitment assistance service (Cline Research) may be considered to facilitate the dissemination of information about the study to the general public, enable online pre-screening, and potentially involve external referral sources.

### 6.3. Overview of Study

For an overview of the intervention, instruments, order of assessment, and moment of assessment, see Figure 1 and Table 1.

## 7. Outcomes and Instruments

### 7.1. Sample Characteristics

General patient characteristics such as age, handedness, educational level, and use of medication will be assessed. The Mini International Neuropsychiatric Interview (MINI) will be used to determine whether the participant has any psychiatric DSM-IV diagnoses.

### 7.2. Primary Outcome Measure

The primary assessment criterion is the PTSD severity score measured using the Clinician-Administered PTSD Scale (CAPS-5) at the one-month follow-up (V13).

### 7.3. Secondary Outcome Measures

PTSD severity scores at M3 and M6 (repetition, avoidance, and neurovegetative activation) measured using CAPS-5 (structured interview);PTSD severity score measured using the PTSD Checklist (PCL-5 self-questionnaire) at M1, M3, and M6;Dissociative symptom severity scores assessed by the Clinician-Administered Dissociative States Scale (CADSS), the Multidimensional Assessment of Interoceptive Awareness (MAIA), and the Dissociative Experiences Scale (DES) at V1, V13, M1, M3, and M6.The severity scores of the dimensions of anxiety (measured using HAM-A) and depression (measured using HAM-D) at M1, M3, and M6.Social cognition at M0 and M3 assessed using the Eckman test, “reading the Mind in the Eyes” test (Baron-Cohen, test des Faux-Pas (Baron-Cohen), Empathy Quotient questionnaire (Baron-Cohen), and Toronto Alexithymia Scale (TAS-20).Quality of life assessed using WHOQOL EuroQol Health Measure, EQ-5D-5L;Proportion of adverse events during the active treatment phase and during the follow-up.

## 8. Statistical Analyses

### 8.1. Power Analysis

The current study is the first to investigate the effect of multiple reactivation therapies enhanced by 20 Hz HF-rTMS sessions on PTSD score severity six months after the last stimulation session. To the best of our knowledge, no studies have investigated the effect of rTMS on PTSD after such a period. A detailed analysis plan will be defined before the database lock. The analysis will be performed by a statistician from URC-Est after data review and database lock. Therefore, no interim analysis is planned. Analyses will be performed using SAS^®^ software (version 9.4 or the updated version).

Based on the literature, we estimate that the CAPS total severity score at M1 in the sham rTMS + memory reactivation procedure group will be at 50 ± 24 (S5 value from [15]). Assuming a 15-point reduction in the experimental group to indicate a clinically significant difference based on the CAPS manual, two-sided alpha = 5% and beta = 15%, and a standard error of 24 in both groups, 92 patients are needed (Student *t*-test, East 6, Cytel). Considering 10% of non-evaluable patients, 102 randomized patients are needed. We anticipate fewer non-evaluable patients than in Kozel’s study (4). Our reactivation memory is less demanding for patients than that of Kozel’s program. Regarding the CAPS score at inclusion, we anticipate a comparable score for the overall severity. This score is close to that reported in Yan’s meta-analysis (3) on the efficiency of rTMS in PTSD. There is empirical evidence regarding the value of prolonged exposure to a wide range of injuries. However, clinical trials have shown that less than 50% of patients improve with exposure therapy and only 15% achieve complete remission [16]. In our study, we will include a more resistant population that is classically less sensitive to the effects of psychotherapy alone. All tests will be two-sided, and a *p*-value of <0.05 will be considered significant.

The baseline characteristics of the patients will be described overall and for each group. Qualitative data will be described with frequencies and percentages and quantitative data will be described with mean and standard error or with median and interquartile interval according to the distribution of the variable.

### 8.2. Primary Criterion Analysis

An analysis will be conducted based on the intent-to-treat (ITT) population.

The CAPS total severity score at M1 will be compared between groups using the Student *t*-test. In the case of a non-normal distribution, transformation will be performed. Sensitivity analyses on available data and on per protocol population using the same methods will be performed.

### 8.3. Secondary Criteria Analysis

PTSD severity scores at V15 and V16 (repetition, avoidance, and neurovegetative activation) measured with CAPS (structured interview) will be described by mean and standard deviation, and the mean difference between groups will be calculated using its 95% confidence interval (CI). Each score (PCLS self-questionnaire, HAM-A, and HAM-D scores) will be analyzed in the same way at V14, V15, and V16. Graphical representations of the evolution over time will be performed. The mean difference between groups and 95% CI will be calculated.

Based on the PTSD severity score measured using the PTSD Checklist (PCLS self-questionnaire), a linear mixed regression model may be performed with the patient as a random effect and the group as a fixed effect. In the case of a non-normal distribution of the interest variable, a transformation will be performed.

Social cognition at V0 and 15 will be assessed by the Eckman test, “Reading the Mind in the Eyes” test [17], Test of Faux-Pas [18], Empathy Quotient questionnaire [19], and Toronto Alexithymia Scale (TAS-20) [20]. The demonstration of cognitive improvement requires a free interval between the end of the active treatment phase and the completion of the assessment. The difference between the M3 and V0 measurements of each test will be calculated using their 95% CI. The evolution of quality of life (assessed using the WHOQOL [21] and EuroQol Health Measure, EQ-5D-5L [22]) will be analyzed. Each subscore of the two scales will be described and analyzed in the same way.

The proportion of at least one adverse event observed during the active treatment phase and during the follow-up will be described and compared between groups using Fisher’s exact test. The proportion difference between groups and their 95% CI will also be calculated. Each type of adverse event will also be described by the group.

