## 1. Background

Post-traumatic stress disorder (PTSD) is defined as a set of symptoms that occur after being exposed to a traumatic incident (re-experiencing the event, avoidance, negative thoughts or sensations, trauma-related arousal, and reactivity). PTSD is ranked as one of the top ten public health issues by the World Health Organization (WHO) [1]. In France in 2014, its frequency was predicted to be 2.4% among civilians [2]. PTSD is frequently a chronic disorder, with just one-third of patients healing after a one-year follow-up and one-third still experiencing symptoms 10 years later [3]. PTSD is associated with significant disability, medical illness, and premature death. The National Comorbidity Survey [3] reports that 16% of PTSD patients have one coexisting psychiatric disorder, 17% have two, and 50% have three or more. Depressive disorders, anxiety disorders, and substance abuse disorders are two to four times more prevalent among individuals with PTSD. Approved therapies are effective in only 41% of patients, even when combined with specific psychotherapy, and the optimal treatment alternatives for non-responding PTSD patients remain unknown. The current mainstay of treatment relies on trauma-focused psychological interventions and psychopharmacological treatments. For most adults newly diagnosed with PTSD, the first-line treatment is trauma-focused psychotherapy that includes exposure, rather than treatment with a serotonergic agent. However, in many cases, a serotonin reuptake inhibitor (SSRI) is a reasonable alternative for patients who prefer medication to psychotherapy or when cognitive-behavioral therapy is unavailable (a frequent situation). Multiple randomized clinical trials [4] have found that patients with PTSD experience reduced symptoms when treated with an SRI compared to a placebo. The majority of PTSD patients receive pharmacological treatment, with antidepressant agents prescribed in 89% of pharmacological treatment cases [5]. Sertraline and paroxetine are the two approved medications [5] and are considered first-line medication treatments for PTSD. However, 41% of subjects fail to respond to antidepressants.

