## 4. Secondary Research Objective

The secondary objectives of this study are to assess the efficacy of brain modulation via 20 Hz rTMS targeting the right dorsolateral prefrontal cortex, in conjunction with simultaneous traumatic memory reactivation, on the following aspects:Different dimensions of PTSD assessed using CAPS-5 at M3 and M6 post-treatment;The severity of PTSD assessed using PCL at each visit;Anxiety symptoms at V13 (end of treatment), M1, M3, and M6 post-treatment;Depressive symptoms at V13 (end of treatment), M1, M3, and M6 post-treatment;Changes in social cognition at M3 post-treatment;Changes in quality of life at M1, M3, and M6 post-treatment;The safety of the intervention.

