#### Exclusion Criteria History of Epilepsy or Seizure

Cochlear implants;Cardiac pacemaker or intracardiac lines, or metal in the body;Strong dissociative tendencies, evidenced by an average score > 20 on the DES;Lifetime psychotic or bipolar disorder;Antisocial personality or borderline personality;Brain injury defined by medical report;Current substance dependence (including alcohol, excluding tobacco);Acute suicidal ideation;No adequate mastering of the French language or no ability to consent;Pregnancy (confirmed by a urine beta-HCG) or breastfeeding;Absence of birth control;Patient under legal protection measures and/or deprived of freedom;Participation in any other interventional study or in the exclusion period of any other interventional study.

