## 9. Discussion

This article presents a multicenter double-blind randomized clinical trial protocol investigating whether 12 sessions of reactivation therapy enhanced by active 20 Hz HF-rTMS, compared with the same reactivation protocol with sham HF-rTMS, improves the treatment outcomes of PTSD. The choice of 12 sessions and 20 Hz was justified by a review of the literature, and in particular by a recent meta-analysis [23], which found several studies to be effective with 12 sessions and also found that the most effective study was Ahmadizadeh’s 20 Hz study [24]. The aim of this study is to decrease symptom severity and improve brain functioning measures, such as social cognition. Participants, who are non-responders to medications, will be offered a promising treatment alternative. The main expected individual benefit would be a regression of core PTSD symptoms: re-experience of the event, avoidance, negative thoughts or feelings, trauma-related arousal, and reactivity. Reducing PTSD symptoms has been largely reported in large cohort studies on morbidity and mortality. An improved quality of life is also expected.

One of the main challenges of this study will be the completion of the entire follow-up procedure since participants will be called at three and six months to assess symptom severity. The strength of this study is that it investigates the effect of multiple HF-rTMS sessions in order to enhance reactivation therapy. So far, only a few studies have looked at neuro-enhanced psychotherapy.

If this study reveals decreased severity scores in the active stimulation group compared with the sham stimulation group, and the active HF-rTMS induces negligible side effects, this may lead to a shift in PTSD treatment and a need for larger clinical trials on neuro-enhanced psychotherapy for other disorders. Furthermore, future studies will be needed to compare the sensitivity and specificity of our protocol against standard treatments. This could eventually result in approval by regulatory authorities as an additional treatment method for PTSD; for instance, the Food and Drug Administration has approved HF-rTMS for the treatment of depression or OCD [25].

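### Section 4, section 7.3, section 8.3 and Table 1 disagree on three sets of secondary outcomes: anxiety and depression at V13, the negative-thoughts group of CAPS-5, and the visits for CADSS, MAIA and DES

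*Protocol article*

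**What the plan says.** **Anxiety and depression.** Section 4 lists among its objectives "Depressive symptoms at V13 (end of treatment), M1, M3, and M6 post-treatment", and gives anxiety the same four time points. Table 1 marks HAM-A and HAM-D at visits 1, 13, 14, 15 and 16. Section 7.3 names these two outcomes at M1, M3 and M6, and section 8.3 analyses them at V14, V15 and V16.

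**CAPS-5 dimensions.** The objective in section 4 is "Different dimensions of PTSD assessed using CAPS-5 at M3 and M6 post-treatment". Section 7.3 turns this into "PTSD severity scores at M3 and M6 (repetition, avoidance, and neurovegetative activation) measured using CAPS-5 (structured interview"), and section 8.3 keeps the same three groups: "PTSD severity scores at V15 and V16 (repetition, avoidance, and neurovegetative activation) measured with CAPS (structured interview"). Section 1 describes PTSD by "re-experiencing the event, avoidance, negative thoughts or sensations, trauma-related arousal, and reactivity". Section 9 describes the main expected benefit as regression of "re-experience of the event, avoidance, negative thoughts or feelings, trauma-related arousal, and reactivity".

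**Dissociation scales.** Section 7.3 makes CADSS, MAIA "and the Dissociative Experiences Scale (DES) at V1, V13, M1, M3, and M6" secondary outcomes. Section 6.3 sends the reader to Figure 1 and Table 1 for the instruments and their timing. Table 1 has no CADSS, MAIA or DES row. DES also serves as an exclusion test: "Strong dissociative tendencies, evidenced by an average score > 20 on the DES".

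**The concern.** Each section is clear when read alone, but together they do not define one set of secondary outcomes. Section 8.3 states the analysis visits and the CAPS-5 groups explicitly. An analyst who follows it gives no between-arm estimate of anxiety or depression at the end of treatment, although an objective asks for one and the data are collected. The same analyst gives no separate estimate for a symptom group in which the authors expect benefit. If either is added once results are known, the addition can be questioned as selective reporting, even though section 4 supports it.

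The dissociation scales raise a different issue. Sections 7.3 and Table 1 give different answers on whether and when they are administered. An analysis can be added later, but an assessment that a site did not make cannot be recovered.

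**Working it through.** No figure in the plan bears on this point, so the check sets the sections side by side. The sample size does not enter. With 24 taken as the standard deviation, 2 × (1.960 + 1.036)² × 24² / 15² ≈ 46 per arm, or 92 in total, as section 8.1 states, and nothing below changes it.

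**Visit labels.** Table 1 gives the last rTMS session at visit 13. Section 4 calls V13 the end of treatment, and section 3 counts one month from the last session. Comparing 7.3 with 8.3 then gives M1 = V14, M3 = V15 and M6 = V16. (Section 7.2 attaches V13 to the one-month follow-up, but that reading does not fit Table 1, where CAPS-5 is given at visits 0, 14, 15 and 16 and not at 13.)

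**(i) HAM-A and HAM-D**

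| Source | V13 | V14 (M1) | V15 (M3) | V16 (M6) |
|---|---|---|---|---|
| Section 4 objective | yes | yes | yes | yes |
| Table 1 collection | yes | yes | yes | yes |
| Section 7.3 outcome | no | yes | yes | yes |
| Section 8.3 analysis | no | yes | yes | yes |

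Comparisons asked for: 2 scales × 4 visits = 8. Planned: 2 × 3 = 6. The two missing are HAM-A and HAM-D at V13, and both are collected.

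**(ii) CAPS-5 symptom groups**

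| Group | Sections 1 and 9 | Sections 7.3 and 8.3 |
|---|---|---|
| Re-experiencing (repetition) | yes | yes |
| Avoidance | yes | yes |
| Negative thoughts or feelings | yes | no |
| Arousal and reactivity (neurovegetative activation) | yes | yes |

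Section 4 names M3 and M6. Possible estimates: 4 groups × 2 visits = 8. Planned: 3 × 2 = 6. The two missing are the negative-thoughts group at V15 and V16. CAPS-5 is collected at both visits.

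**(iii) CADSS, MAIA and DES**

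Section 7.3: 3 scales × 5 visits (V1, V13, M1, M3, M6) = 15 scale-by-visit assessments. Table 1 marks none of the 15. The other scales and cognitive tests in 7.3 can all be found in Table 1, with the tests attributed to Baron-Cohen sharing a row besides the separate Empathy Quotient row. These three are therefore the exception among the rating instruments.

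**The case against.** The case on the other side is substantial, and several stronger readings fail against it.

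- **CAPS-5 dimensions at M1.** A reader might infer that these are missing too, since CAPS-5 is given at V14. The documents do not support that. Sections 4, 7.3 and 8.3 all give M3 and M6 for the dimensions, and M1 belongs to the total score as primary outcome. Analysing dimensions at M1 would be an option, not the repair of an omission.
- **The negative-thoughts group as a named outcome.** It is not one. It appears in the background and the discussion, and 7.3 and 8.3 agree with each other. The primary analysis of the total severity score also stands. This part of the objection holds to the extent that the mismatch lies between the unrestricted objective and the three-group list, not between 7.3 and 8.3. It does not remove the mismatch, because a total score gives no separate estimate for the group.
- **Nothing analysed at the end of treatment.** This would be too broad. PCL-5 is collected at V13, section 8.3 allows a mixed model on it and plans graphs over time, and adverse events in the active phase are compared between arms. The gap is the HAM-A and HAM-D comparison at one visit.
- **No dissociation data will be collected.** Table 1 is an overview, Figure 1 is not shown, and 7.3 itself states the visits. Table 1 also has no row for adverse events, which are plainly to be recorded. Absence from the table does not prove absence from the trial. What stands is that the two places disagree.
- **Patients above the DES cut-off will be admitted.** The documents do not support this. The exclusion criterion is stated, section 6.1 requires the investigator to verify eligibility, and 7.3 places DES at V1, before the first rTMS session at visit 2.
- **The missing analysis method for dissociation.** Section 8.1 promises a detailed analysis plan before database lock, so the method may be given there. It is not counted here.

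**Conclusion.** Three inconsistencies stand, all within the article itself. HAM-A and HAM-D at V13 are an objective and are collected but not analysed (2 of 8 comparisons). The negative-thoughts group of CAPS-5 is left out of the dimension analysis at M3 and M6 (2 of 8 estimates). CADSS, MAIA and DES are outcomes at five visits in 7.3 and at none in Table 1 (15 scale-by-visit assessments).

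It would be too strong to say that stated objectives go unanswered. Anxiety and depression are still compared at three visits, three of the four symptom groups are still estimated, and dissociation is an outcome in 7.3 but not an objective in section 4.

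The counts rest on two readings. The first is the visit mapping shown above. The second is that arousal and reactivity form one group matching neurovegetative activation; if they were counted separately the denominator would rise, but negative thoughts would still be absent. This is a secondary-outcome matter that should be settled before the analysis plan is final.

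**What to change.** 1. In 7.3 and 8.3, add V13 to the HAM-A and HAM-D outcomes, with the same between-arm estimate and 95% confidence interval as at V14 to V16.
2. In 7.3 and 8.3, add the negative thoughts/mood group to the CAPS-5 dimensions at V15 and V16, so that the list matches the objective in section 4.
3. Reconcile 7.3 with Table 1 on CADSS, MAIA and DES. Either add rows at the visits that 7.3 names, including the DES assessment used for eligibility, or remove from 7.3 the scales that will not be collected as outcomes. If DES is removed as an outcome, its use at screening should still be shown in the schedule.

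Items 1 and 2 cost a few words and four more estimates (2 + 2) from data already scheduled. Item 3 costs up to three table rows, or a deletion. It introduces no instrument that 7.3 does not already name, and adds to patients' visits only if sites have been working from Table 1 alone.

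### CAPS-5 at M3 and M6 is compared by an unadjusted mean difference at each visit, which ignores the baseline and M1 scores and may be biased if withdrawal after M1 relates to outcome

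*Protocol article*

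**What the plan says.** Section 4 lists as its first secondary objective "Different dimensions of PTSD assessed using CAPS-5 at M3 and M6 post-treatment". Section 8.3 gives the analysis: the dimension scores at V15 and V16 "will be described by mean and standard deviation, and the mean difference between groups will be calculated using its 95% confidence interval (CI". The PCL, HAM-A and HAM-D scores are handled the same way at V14, V15 and V16. Section 8.3 and Table 1 imply that V14 is M1, V15 is M3 and V16 is M6, and that numbering is used here.

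The one longitudinal model in 8.3 concerns the PCL: "a linear mixed regression model may be performed with the patient as a random effect and the group as a fixed effect". No visit term and no group-by-visit term is stated.

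For the primary criterion, section 8.2 says "An analysis will be conducted based on the intent-to-treat (ITT) population" and adds "Sensitivity analyses on available data and on per protocol population using the same methods will be performed". Section 8.3 names no analysis population and no rule for missing scores.

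On follow-up, section 9 says "One of the main challenges of this study will be the completion of the entire follow-up procedure" and refers to the three- and six-month assessments. Section 8.1 presents as new in this trial the effect "on PTSD score severity six months after the last stimulation session", and leaves detail to an analysis plan to be written before database lock.

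**The concern.** A raw difference in means at one visit contains only that visit's scores. Without imputation, a patient assessed at V0 and V14 who then withdraws contributes nothing at M3 or M6. Yet the M1 score is in hand and may well be related to why the patient left. If patients who are still unwell at M1 leave to seek other treatment, an effective treatment alone makes the losses unequal, with more high scorers leaving sham. If patients who feel well stop attending, the pattern differs. Either way, the groups compared at M6 need no longer be the groups that randomisation made comparable.

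At stake is the estimate of how long the effect lasts, which section 8.1 presents as the novel part of the trial. CAPS-5 is the trial's main instrument, and it is the one for which 8.3 offers no longitudinal model. The optional PCL model would not fill the gap for the PCL either: with group as the only fixed effect, it gives one average arm difference and none specific to M6.

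**Working it through.** **1. The plan's own figure.** Section 8.1 gives SD 24, difference 15, two-sided alpha 5% and power 85%. By the normal formula, n per arm = 2 × (1.960 + 1.036)² × 24² / 15² = 2 × 8.98 × 2.56 = 46, so 92 in total, as stated. With the 10% allowance, 92 / 0.9 = 102.2, and the plan randomises 102. These figures concern M1. No loss rate is given for M3 or M6.

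**2. Inputs for the illustration.**
- From section 8.1: total-score means of 50 (sham) and 35 (active, 50 − 15), SD 24.
- Assumed, because the document gives no figure: the same means and SD at M6; M1–M6 correlation 0.6 to 0.8; overall loss after M1 of 20% or 30%; log-odds of withdrawal rising by 0.7 to 1.5 per SD of the M1 score, under one rule for both arms.

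**3. One rule on the actual M1 score.** M1 and M6 scores were simulated as bivariate normal in very large samples. Withdrawal was drawn from logit P = a + b × (M1 score in SD units). The M6 means were then compared in two ways.

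| Quantity | Result |
|---|---|
| Loss, sham | 23% to 37% |
| Loss, active | 14% to 26% |
| Observed-only difference at M6 (true 15) | 12.3 to 14.5 |
| Difference after regressing M6 on M1 within arm and averaging over all patients | about 15 (14.9 to 15.1) |

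At 10% overall loss, the observed-only difference is about 13.5 to 14.6.

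**4. Other mechanisms.** Here withdrawal depends on the M1 score relative to the arm's own mean (log-odds 1 per SD), with loss 10–30% and correlation 0.5 or 0.7.

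| Mechanism | Observed-only difference |
|---|---|
| Unrelated to M1, or same dependence in both arms | about 15 |
| High scorers leave active; loss in sham unrelated to score | 16.1 to 19.3 |
| High scorers leave sham, low scorers leave active | 12.8 down to 6.5 |
| High scorers leave active, low scorers leave sham | 17.2 to 23.6 |

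The M1-conditioned estimate stays at 14.9 to 15.1 throughout. The bias therefore ranges from none to about 9 points, in either direction.

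**5. Precision.** The 95% half-width of the raw difference is t × 24 × √(2/m), with m = 51 × (1 − loss). It is 9.4 with no loss, and 10.0, 10.6 and 11.3 at 10%, 20% and 30% loss. If loss is unrelated to score, using the M1 score multiplies this by about √(1 − ρ² × loss). At 30% loss and ρ = 0.8 the factor is √(1 − 0.64 × 0.3) = 0.90, so 11.3 becomes 10.2. At 20% loss and ρ = 0.6 it is √(1 − 0.36 × 0.2) = 0.96, so 10.6 becomes 10.2. Adjustment for baseline CAPS-5 would add to this, by an amount the document does not allow one to compute.

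**The case against.** A reader might infer that the protocol commits to analysing only patients who attend at M3 and M6. It does not say so. Section 8.3 gives a summary measure without an analysis set, and a mean difference can also be computed after imputation. Section 8.2 lists the available-data analysis separately from the ITT analysis, so the authors know the distinction. The article is condensed and defers to an analysis plan, where missing-data handling commonly sits. All of this stands: silence on missing data is not the finding.

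A reader might also infer that the M3 and M6 results will be biased. That too goes beyond the document, which gives no loss rate, mechanism or correlation. Under some mechanisms the bias is nil. Under the single-rule mechanism it is at most 2.7 points (15 − 12.3) and towards zero, well inside a half-width of 10.6 to 11.3. The illustration also uses the total score, whereas 8.3 speaks of dimension scores.

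Finally, these are secondary results for which 8.3 names estimates and intervals but no test.

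These points limit the size and certainty of the concern. They do not remove it, because the estimator itself is stated in 8.3: it leaves out the baseline and M1 scores, and a better one is available from data already scheduled.

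**Conclusion.** The point holds in conditional form. The CAPS-5 comparison fixed for M3 and M6 is an unadjusted per-visit difference. Unless the analysis plan adds missing-data handling, it rests on observed scores and may be biased if withdrawal after M1 relates to the M1 score. Under the single-rule assumptions above, the observed-only difference is about 12 to 14.5 points against a true 15. If withdrawal acts differently by arm, the error can be larger and go either way. The loss of precision is modest, about 4% to 10% of the interval width at 20–30% loss. The sizes rest on assumed loss, correlation and mechanism, and on a 15-point difference carried to M6.

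It would be too much to conclude that the trial's main result is in doubt: the primary comparison is at M1 and is not affected. Nor does the document make a confirmatory claim of a lasting effect; the six-month sentence in 8.1 describes novelty. This is a change worth making before database lock, not a fatal fault.

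**What to change.** In section 8.3 and in the analysis plan:

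- Estimate the CAPS-5 arm differences at V15 and V16, with 95% CIs, from one likelihood-based repeated-measures model over V14, V15 and V16. Include arm, visit, arm-by-visit, baseline CAPS-5 (V0) and site, the last because randomisation is stratified by site. Include all randomised patients with any post-baseline score.
- Use the analogous model for HAM-A and HAM-D on their own schedule in Table 1 (baseline V1; V13 to V16).
- Keep raw means and SDs as description, and report the number assessed per arm at each visit.
- Add a simple sensitivity analysis for departures from missing at random, for example shifting the unobserved scores by a range of fixed amounts in each arm.

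The cost is wording and a little more programming. Table 1 already schedules CAPS-5 at V0, V14, V15 and V16, so no visit or measurement is added. The model relies on missing at random, which is a weaker assumption than the one that the observed-only raw difference needs; the sensitivity analysis covers what remains.
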